### Outcome assessment

The variables in this trial consist of basic characteristics, primary outcomes and secondary outcomes. The basic characteristics will be measured at baseline, and primary and secondary outcomes will be measured at baseline and at the end of each intervention period (3, 6 and 12 months after randomisation). All of the primary and secondary outcomes will be assessed by experienced staff at each sleep centre who will be blinded to treatment allocation.

### Basic characteristics

Participants’ basic characteristics (eg, age, sex, years of education, medical history, medication use and occupation) will be gathered by recruiters using a questionnaire. The two standardised neurobehavioural scales, such as Montreal Cognitive Assessment (MoCA) and MMSE scores will be assessed. The assessors in each sleep centre will be trained by a neurologist. Before randomisation, all baseline assessment will be finished.

### Primary and secondary outcomes

#### Primary endpoints

MoCA.

#### Secondary endpoints

MMSE.

Default mode network and cortical thickness are measured by functional and structural MRI.

Cerebral metabolites, such as N-acetylaspartate (NAA), choline (Cho), creatine (Cr), glutamate and glutamine and myo-inositol are measured by magnetic resonance spectroscopy (MRS).

Neuropsychological tests will also be performed, including mental arithmetic, memory scanning, movement perception, switching attention, space location memory span and attention allocation choice reaction time curve fit.

Sleep variables include AHI, oxygen desaturation index, lowest oxygen saturation, mean oxygen saturation, micro-arousal index, total sleep time, total REM sleep time, total slow wave sleep time, etc.

#### Auditory testing

Central auditory processing tests performed include speech-in-noise test, competing sentences test, gap detection and dichotic listening.

Data were recorded using 256-channel high-density electroencephalograph (EEG) recordings.

The gut microbial community will be quantified using metagenomics analysis.^25^ Low-molecular-weight metabolites (≤1000 kDa) will be quantified by metabolomics analysis.^26^

Amyloid-β protein 42, presenilin 1, amyloid-β protein 40, total GSK-3β and serine-9 phosphorylated GSK-3β

#### Other outcomes

##### Biochemical variables

Biochemical variables include lipid profile (total cholesterol, triglycerides, high-density lipoprotein cholesterol, low-density lipoprotein cholesterol, apoA-I, apoB, apoE and lipoprotein(a)), glucose, insulin, HbA1c, free fatty acids, cholinesterase, lipopolysaccharide-binding protein, toll-like receptor-4, TLR-2, hepatic function tests (alanine aminotransferase, aspartate aminotransferase, γ-glutamyl endopeptidase, alkaline phosphatase, total protein, albumin, total bilirubin, direct bilirubin, bile acid, prealbumin), renal function tests (creatinine, urea nitrogen, uric acid), microalbuminuria and apolipoprotein E genotyping.

##### Inflammatory biomarkers

Inflammatory biomarkers include leptin, regulated on activation, normal T cell expressed and secreted, monocyte chemotactic factor 1, interleukin (IL)-6, IL-8, tumour necrosis factor-α, hypersensitive C-reactive protein, resistin, serum amyloid A protein and α-acid glycoprotein.

##### Anti-inflammatory biomarkers

Anti-inflammatory biomarkers include adiponectin and IL-1Ra.

##### Oxidative stress index

Oxidative stress index may include: 8-isoprostane, blood pressure (systolic blood pressure and diastolic blood pressure), anthropometric variables (weight, height, waist, hip, chest and neck circumferences, visceral fat area and subcutaneous fat area), echocardiography, arterial stiffness (pulse wave velocity, ankle brachial index and toe-brachial index), lung function (eg, forced expiratory volume in 1 s and forced vital capacity) and ECG.

#### Study examination procedures

All of the study measurements will be performed before and after 3, 6 and 12 months of CPAP intervention at each centre, except for lung function and ECG.

##### Anthropometric measurements

Height and weight will be measured using standard methods. BMI (weight (kg)/height^2^ (m^2^)) will be calculated from height and weight. Waist, hip and neck circumferences will be measured using a measuring tape in the conventional manner.

##### Urine samples

First midstream urine samples will be collected in the morning with the collected urine samples stored immediately at –80°C for further analyses.

##### Blood samples

Fasting blood samples will be collected in the morning, and the samples will be immediately sent for further analyses such as biochemical analysis.

##### Faecal samples

Faecal samples will be collected and stored at –80°C until use in subsequent assays. The composition of microbiota will be measured using 16S rRNA-hybridisation and DNA staining.

##### Sleep respiratory variables

Laboratory-based PSG (Alice 4 or 5, Respironics; Pittsburgh, PA, USA) will be used to record sleep parameters. EEG, electrooculography, ECG, electromyography, nasal/oral airflow, thoracic/abdominal movement, pulse oximetry, body posture and snoring will be recorded. The definition of OSA is established according to the AASM 2007 criteria.

##### Neuropsychological tests

Two standardised questionnaires (MoCA and MMSE) will be administered. Neuropsychological tests will also be performed, including mental arithmetic, memory scanning, movement perception, switching attention, space location memory span and attention allocation choice reaction time curve fit.

##### Auditory testing

Audiograms will be measured in one-octave steps at frequencies ranging from 125 Hz to 8 kHz and then at 10, 12.5, 16 and 20 kHz. DPOAE values will be recorded in both groups using a Madsen Capella cochlear emissions analyser in a soundproof room. Only patients with normal audiometry (threshold below 25 dB HL at all frequencies from 0.125 to 20 kHz), normal DPOAE levels, normal tympanometric curve of type A and presence of ipsilateral and contralateral stapedial reflexes will be included.

##### Central auditory processing testing

The following central auditory processing tests will be performed in a soundproof room. Before the formal test, participants will be allowed to practice as many times as required and provide feedback to become familiar with the stimuli. (1) Speech-in-noise test: all of the signal processing will be performed with MATLAB software. The speech of 20 ten-word sentences will be presented under both quiet and noisy conditions with speech-shaped noise and will be delivered bilaterally through Sennheiser HD205 headphones at a signal:noise ratio of –5 dB. (2) Competing sentences test: babble noise and the target sentence will be presented bilaterally at an intensity level of 65 dB SL (above speech reception threshold) at a signal:noise ratio of –3 dB. (3) Gap detection: the purpose of this evaluation is to determine the smallest interval that the listener can detect. Two stimuli separated in time by a ‘gap’ will be presented, and the listener will be asked to detect the gap, essentially discriminating sound from silence. Stimuli as white noise will be bilaterally presented as background noise at intensities 40 dB higher than the hearing threshold. (4) Dichotic listening: two different numbers will be simultaneously presented to both ears with the subjects instructed to repeat both numbers in any order. The test includes 20 number pairs presented dichotically. The number pairs will be aligned for onset and offset to eliminate any cue for the first number heard. Dichotic listening performance will be scored as the percentage of correctly reported different numbers from the right and left ears in the noise-exposed and control groups.

##### 256-Channel high-density EEG recording

EEG data will be recorded with 256 channels on an EGI HydroCel Geodesic Sensor Net, with Cz used as the reference channel. All of the electrode impedances will be detected and maintained at less than 50 kΩ. The oddball stimuli pattern with speech sound is used in this study (via Eprime V.2.0; Psychology Software Tools). The auditory oddball task includes presentation sound of /Ba/, whereas /Da/ is presented as the ‘oddball’ target stimulus. The stimulus /Ba/ is presented in 85% of the trials together with the stimulus /Da/ in 15% of the trials. The whole task consists of a total of 1000 auditory stimuli with random interstimulus intervals ranging from 850 ms to 1450 ms. The sound stimuli with an intensity of 75 dB delivered through two loudspeakers at a distance of 100 cm from the subjects. During the P3 cortical waves test, the subjects will be asked to press a switch held in the right hand each time they detect a target tone with the eyes closed. In addition, they will be asked not to respond to any auditory stimulus while watching silent films during the MMN test. Source analysis of event-related potentials as MMN, describing neural sources of measured scalp potentials, will be estimated with GeoSource V.2.0.

##### Brain imaging

MRI will be performed using the Siemens 3T Verio scanner (MAGNETOM, Siemens) with a 12-channel coil using the same parameters. High-resolution T1-3D-weighted and T2-3D-weighted MRI sequences will be conducted for all subjects. *T1-3D axial images*: field of view (FOV), 230 mm; repetition time (TR)/time to echo (TE), 1500/2.96 ms; flip angle, 9°; voxel size, 0.9×0.9×1 mm^3^; slice thickness, 1 mm; and distance factor, 50%. *T2-3D axial images*: FOV, 230 mm; TR/TE, 1500/2.96 ms; voxel size, 0.9×0.9×1 mm^3^; slice thickness, 1 mm; and distance factor, 50%. In the same position, a s-fMRI BOLD sequence will be acquired in the rest condition, and 240 functional images will be obtained (repetition time 2000 ms, echo time 30 ms, thickness 4.0 mm, gap 1.2 mm, acquisition matrix 64×64, flip angle 90°, field of view 230×230 mm^2^, 30 axial slices with gradient-recalled echo-planar imaging pulse sequence covering the whole brain). Patients will be asked to keep their eyes closed and not to focus their thoughts on any particular topic or to fall asleep. Diffusion kurtosis imaging will be performed in all subjects using 30 gradient directions, six b values and an echo-planar diffusion-weighted imaging sequence. FOV, 300 mm; TR/TE, 1100/109 ms; matrix size 128×128; and slice thickness 4 mm.

##### Cerebral metabolites

MRS will be performed using the Siemens 3T Verio scanner with a 12-channel coil. A 2.0×2.0×2.0 cm^3^ voxel of interest will be placed at the frontal lobe. NAA, Cho and Cr will be acquired by a MEGA-PRESS sequence using the following parameters: TE/TR=135/5000 ms; average number 80 (scan time 8 min).

##### Abdominal and liver fat measurements

The hepatic, subcutaneous and visceral fat will be measured by axial scanning of the upper abdomen (from the diaphragm to the lower edge of the liver). The participants will be instructed to hold their breath to reduce the artefacts induced by respiratory movement. Anatomical T1-weighted spin-echo MRI will be obtained using the following parameters: slice thickness 5 mm; slice spacing 2.5 mm.

### Safety measurements

Any unexpected adverse events associated with CPAP intervention during OSA-treatment period will be monitored and then reported. The severity and causality of adverse events should also be analysed. The data we submit will be monitored by the Ethics Committee of Shanghai Jiao Tong University Affiliated Sixth People’s Hospital. If serious adverse events occurred, they should be immediately reported to the aforementioned ethics committee.

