### Withdrawal criteria

Subjects will be permitted or required to withdraw from this study if they have insurmountable claustrophobia or other unbearable conditions associated with CPAP use, major protocol violation or the development of serious systemic diseases that prevents continuation in this study.

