### Randomisation, allocation concealment and blinding

All eligible patients with moderate to severe OSA will be randomly and equally allocated (randomisation ratio 1:1) to the CPAP plus BSC group or BSC only group. The central random allocation sequence will be produced using the statistical software SAS V.9.4 and managed by an independent statistician (from the Department of Epidemiology, School of Public Health, Shanghai Jiao Tong University) who will be blinded to the participants’ recruitment, evaluation and intervention. The research assistant from each sleep centre will request (via email) a participant’s allocation from the statistician. The group allocation will not be blinded by participants or intervention supervisors in this trial; however, the patients’ group assignments can be blinded to result assessors and statisticians (ie, which patients are allocated to the CPAP treatment versus BSC groups will not be disclosed).

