### Intervention

#### BSC only group

Participants in the BSC only group will receive advice regarding lifestyle modification, sleep hygiene, naps, exercise, caffeine and diet and avoiding alcohol consumption, but no specific weight loss programme, diet or salt restriction will be suggested.

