### Follow-up

At 3, 6 and 12 months during the intervention period, all of the participants will undergo the same examinations as at baseline. During the follow-up period, CPAP usage information will be automatically downloaded daily from auto CPAP via the Internet.

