### Sample size calculation

A previous study indicated that the mean and SD of MoCA score are 26.1 (2.0) and 27.4 (2.3) before and after CPAP treatment, respectively.^27^ With a significance level of 0.05 and statistical power of 0.9, the calculated sample size is 59 for each group. Considering a 20% loss to follow-up, a total of 148 participants will be required for randomisation.

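### Routine adverse-event monitoring covers only unexpected, CPAP-associated events, so non-serious adverse events cannot be compared fairly between the arms

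*Protocol article*

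**What the plan says.** The Safety measurements section of the protocol article is short. Its statement of what is monitored is: "Any unexpected adverse events associated with CPAP intervention during OSA-treatment period will be monitored and then reported". It then adds "The severity and causality of adverse events should also be analysed", names an ethics committee as monitor of the submitted data, and ends with "If serious adverse events occurred, they should be immediately reported to the aforementioned ethics committee".

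Three other sections bear on the point.

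- **Randomisation, allocation concealment and blinding:** patients are "randomly and equally allocated (randomisation ratio 1:1) to the CPAP plus BSC group or BSC only group".
- **BSC only group:** the comparator is advice. "Participants in the BSC only group will receive advice regarding lifestyle modification, sleep hygiene, naps, exercise, caffeine and diet"; no CPAP is given.
- **Withdrawal criteria:** CPAP intolerance is foreseen, but only as grounds for leaving the study, in the words "insurmountable claustrophobia or other unbearable conditions associated with CPAP use".

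Both arms keep the same visit schedule (Follow-up): "At 3, 6 and 12 months during the intervention period, all of the participants will undergo the same examinations as at baseline".

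**The concern.** The monitoring sentence applies three filters before an event counts: it must be unexpected, it must be associated with CPAP, and it must fall in the treatment period. In a two-arm trial where only one arm has CPAP, the second filter makes capture of non-serious events depend on allocation. The first filter removes the effects that CPAP users are most likely to report, because they are already known.

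The result would be a safety table whose BSC column is empty by definition and whose CPAP column omits the familiar complaints. A reader could take the empty column to mean that nothing happened in patients with moderate to severe OSA followed for 12 months without CPAP. A reader could equally take the short CPAP column to mean good tolerability. The rule as written supports neither conclusion.

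**Working it through.** **Step 1. Size of each arm.** The Sample size calculation section uses "mean and SD of MoCA score are 26.1 (2.0) and 27.4 (2.3) before and after CPAP treatment, respectively", alpha 0.05, power 0.9 and 20% loss.

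- Difference: 27.4 − 26.1 = 1.3.
- Pooled SD: √((2.0² + 2.3²)/2) = √4.645 = 2.155.
- Normal approximation: n = 2 × (1.960 + 1.282)² × 4.645 / 1.3² ≈ 57.8, so 58 per group. The t-test version gives 58.7, so 59, as stated.
- Allowing for loss: 59 / (1 − 0.2) = 73.75, so 74 per arm and 148 in total, as stated.

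The plan's figure reproduces, and nothing in it depends on how adverse events are defined. It is used here only for the arm size of 74.

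**Step 2. The rule applied to each kind of event.**

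| Event | CPAP plus BSC arm | BSC only arm |
|---|---|---|
| Serious, any cause | Reportable | Reportable |
| Non-serious, unexpected, CPAP-associated | Monitored | Cannot arise |
| Non-serious, expected, CPAP-associated, participant stays in | Outside the rule | Cannot arise |
| CPAP-associated and ends participation | Visible as a withdrawal | Cannot arise |
| Non-serious, not CPAP-associated | Outside the rule | Outside the rule |

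The only row of non-serious events that the rule captures is one that BSC participants cannot enter. No row of non-serious events is captured in both arms, so there is no common basis for comparing them. The serious row is the same in both arms.

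**Step 3. Order of judgement.** The section wants causality analysed, yet the monitoring sentence admits only events already linked to CPAP. A causality analysis of events selected on causality tells little. It needs the unselected set.

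**Step 4. Scale, by assumption only.** The documents give no adverse-event rates. The table takes assumed 12-month risks of 1%, 2% and 5% for some non-serious event among the 74 BSC participants.

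| Assumed risk | Expected cases (74 × risk) | Chance of at least one case, 1 − (1 − risk)^74 |
|---|---|---|
| 1% | 0.74 | 52% |
| 2% | 1.48 | 78% |
| 5% | 3.70 | 98% |

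The rule as written would record none of these. With full capture, observing none would be informative: the rule of three puts the upper 95% limit at 3/74 = 4.1%, or 3/59 = 5.1% if only 59 are followed to the end. Without capture, a zero carries no such limit.

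Full capture would not make this a powerful safety trial. With 74 per arm, the power to separate assumed risks of 5% and 15% is about 53%, and for 10% and 30% about 87%. The gain is an unbiased description by arm rather than a sensitive test.

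**The case against.** The strongest reply is that this is a condensed article. The sentence does not say that only these events are recorded, and case-report-form content is usually left to the full protocol, which is not shown. The sentence on severity and causality names no arm. The trial has no comparative safety objective. Some harms would also be seen elsewhere: blood pressure, echocardiography, arterial stiffness and biochemistry are outcomes in both arms, CPAP use is downloaded daily, and severe intolerance shows as withdrawal.

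Part of this stands. It cannot be said that other events are certainly left off the forms, and the outcome measures give indirect sight of cardiovascular and metabolic harm. But the monitoring sentence is a stated scope with explicit qualifiers, not a gap that a fuller document would simply fill. If the full protocol collects everything, this sentence misdescribes it and still needs correcting. The severity and causality sentence concerns analysis and does not widen what is collected. The outcome measures are not labelled as safety data and do not replace event records.

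Three stronger readings are tempting, and the documents do not support them.

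- **That no safety comparison between arms is possible.** The serious-event sentence has no restriction by arm, expectedness or relation to CPAP, so serious events can be compared.
- **That attribution to CPAP is made with allocation known.** The section does not say who judges it. Intervention supervisors know the allocation, but Data collection and management says that data collectors and evaluators are blinded, and nothing assigns the judgement to either group.
- **That the ethics committee would see no non-serious events from the BSC arm.** The section does not define which data are submitted to it.

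**Conclusion.** The point holds for non-serious adverse events. As worded, the rule takes in unexpected CPAP-associated events and leaves out non-serious events in the BSC only arm, together with expected, non-serious CPAP effects that do not lead to withdrawal. These events therefore cannot be compared fairly between arms. Serious adverse events are outside the criticism.

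The rule affects all 74 BSC participants, and the expected-effect part affects the 74 allocated to CPAP. The number of events missed cannot be derived from the documents; the 1% to 5% risks in the working are assumptions that illustrate scale. The primary analysis and the sample size are untouched. The conclusion assumes that sites follow the sentence as written. The change should be made because the bias is built into collection and cannot be repaired at analysis.

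**What to change.** Reword the monitoring sentence in Safety measurements along these lines: all adverse events, expected or not and whatever their suspected cause, will be recorded in both arms with the same form and the same questions at 3, 6 and 12 months; expectedness, severity and causality will be judged afterwards and held as separate fields; events will be reported by randomised arm. The immediate reporting of serious events stays as it is.

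Two practical points go with it. Events such as mask problems reveal allocation, so the form should be completed by someone other than the blinded outcome assessor, or after the cognitive assessment. Enrolment was already under way when the article was submitted, so the report should state from what date the common form was used and separate events recorded before it.

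The cost is slightly more data entry at visits that both arms already attend, on case report forms already in use. No change to sample size or visit schedule is needed.

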### Sample size calculation

A previous study indicated that the mean and SD of MoCA score are 26.1 (2.0) and 27.4 (2.3) before and after CPAP treatment, respectively.^27^ With a significance level of 0.05 and statistical power of 0.9, the calculated sample size is 59 for each group. Considering a 20% loss to follow-up, a total of 148 participants will be required for randomisation.

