#### CPAP plus BSC group

Participants in the CPAP plus BSC group will receive CPAP treatment plus the aforementioned BSC intervention. CPAP treatment (LOTUS AUTO; Curative Medical Technology, Beijing, China) will be initiated using standard clinical practice (before CPAP treatment, the standard clinical practice is for the doctors to educate patients on the use of CPAP and provide positive encouragement) at each centre. Online monitoring of CPAP compliance can also be used to improve compliance. Participants in both groups will be asked to continue their usual medical care during the trial.

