### Statistical methods

The statistical analysis in this trial will be performed using intention-to-treat (ITT). For missing data, a multiple imputation method will be performed. Normality of the data distribution will be examined by the Kolmogorov-Smirnov test. Continuous variables will be expressed as mean±SD or median (first to third quartile) for normal distribution data or non-normal distribution data, respectively. Categorical variables will be expressed as percentages. To assess primary and secondary endpoints in this trial, a mixed-effects linear model under restricted maximum likelihood and a logistic regression model will be used to analyse the effect of CPAP treatment on the continuous or categorical variables, respectively. In each model, the independent variables should include group (CPAP plus BSC group and BSC group), confounding factors (eg, age, BMI and waist:hip ratio, etc), measurement time (eg, baseline and 3-month, 6-month and 12-month follow-ups) or any other inequality factors between groups at baseline assessment. When a significant main effect was observed, a *post hoc* comparison for different time points (eg, baseline and 3-month, 6-month and 12-month follow-ups) or between groups (CPAP plus BSC group and BSC group) will be performed using multiple comparisons. All of the statistical analyses will be performed using SAS V.9.4, with a two-sided p value<0.05 indicating a statistical significance.

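### The sample size takes a within-CPAP before-after MoCA change as the CPAP-versus-BSC difference, so the stated 90% power assumes that the BSC arm does not improve

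*Protocol article*

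**What the plan says.** The Sample size calculation section gives a single empirical basis: "A previous study indicated that the mean and SD of MoCA score are 26.1 (2.0) and 27.4 (2.3) before and after CPAP treatment". It continues: "With a significance level of 0.05 and statistical power of 0.9, the calculated sample size is 59 for each group". The total follows from attrition: "Considering a 20% loss to follow-up, a total of 148 participants will be required for randomisation". The section gives no MoCA mean for BSC, no expected change under BSC and no between-group difference.

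The comparison to be tested is between randomised arms. Patients are to be "randomly and equally allocated (randomisation ratio 1:1) to the CPAP plus BSC group or BSC only group", and the primary hypothesis under Study aims and hypotheses is worded against the group without CPAP. MoCA is the only primary endpoint. BSC is common to both arms: "Participants in the CPAP plus BSC group will receive CPAP treatment plus the aforementioned BSC intervention". Under BSC only group it is described as advice on lifestyle, sleep hygiene, exercise, diet and alcohol, among other things. Under Follow-up, at 3, 6 and 12 months, "all of the participants will undergo the same examinations as at baseline".

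**The concern.** A change from before to after CPAP is a different quantity from the difference between a CPAP arm and a concurrent control arm. The before-after change includes whatever would have happened without CPAP, such as a gain from taking the MoCA again or a drift over time. In a randomised comparison, any such component also occurs in the BSC arm and cancels. Here the control arm also receives active advice. If 1.3 is the change in the CPAP arm, the between-arm difference is 1.3 minus the gain in the BSC arm. It equals 1.3 only if that gain is zero.

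The 90% power is the stated justification for 148 participants. If the BSC arm improves, the randomised comparison has less power than the protocol reports, and a non-significant result on the primary endpoint would carry less information than that figure suggests.

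**Working it through.** **Inputs**

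- Means and SDs from Sample size calculation: 26.1 (2.0) and 27.4 (2.3); difference 27.4 − 26.1 = 1.3.
- Significance level 0.05 and power 0.90, from the same section. The test is taken as two-sided because Statistical methods says so: "with a two-sided p value<0.05 indicating a statistical significance".
- Allocation 1:1; loss to follow-up 20%.
- BSC gain and pre-post correlation: not given in the document. The values used below are assumptions.

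**Reproducing the plan's figure**

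Pooled SD = √[(2.0² + 2.3²)/2] = √4.645 = 2.155. Standardised difference = 1.3/2.155 = 0.603.

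Normal approximation: n = 2(1.960 + 1.282)² × 4.645/1.3² = 57.8, so 58 per group. The two-sample t-test (noncentral t) gives 89.6% power at 58 and 90.1% at 59, so 59 per group. Attrition: 59/0.8 = 73.75, so 74 per group and 148 in total. Both stated figures are reproduced.

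The alternatives tried do not give 59. By normal approximation, a one-sided test gives 48 per group, SD 2.0 gives 50 and SD 2.3 gives 66. A paired before-after test gives 41 subjects at a correlation of 0.3 and 18 at 0.7. The pre-CPAP value was therefore used as the control arm and the post-CPAP value as the treated arm.

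**Margin in that calculation**

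With 59 per arm and SD 2.155, the standard error is 2.155 × √(2/59) = 0.397. The t-test needs a true difference of 1.297 for 90% power and 1.12 for 80%. There is almost no room below 1.3.

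**Power with 59 evaluable per arm if the BSC arm gains c points**

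True difference = 1.3 − c. For the baseline-adjusted columns, the SD is 2.155 × √(1 − r²), where r is the assumed correlation between baseline and follow-up.

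| Assumed c | Difference | Unadjusted | r = 0.3 | r = 0.5 | r = 0.6 | r = 0.7 |
|---|---|---|---|---|---|---|
| 0 | 1.3 | 90.1% | 92.6% | 96.3% | 98.2% | 99.5% |
| 0.1 | 1.2 | 85.1% | 88.2% | 93.4% | 96.3% | 98.7% |
| 0.3 | 1.0 | 70.5% | 74.5% | 82.3% | 87.8% | 93.8% |
| 0.5 | 0.8 | 51.6% | 55.4% | 63.6% | 70.5% | 79.9% |

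If the larger SD of 2.3 is used for the adjusted analysis, the gain is smaller. At r = 0.6 the four rows become 96.8%, 94.0%, 83.3% and 64.9%; at r = 0.3 the first row is 89.1%.

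**The case against.** The strongest reply is that the sample-size formula is not the planned analysis. Statistical methods specifies a mixed-effects model with baseline and three follow-up times plus covariates, and such a model can use the within-patient correlation that the formula ignores. That conservative element partly offsets the optimistic effect size. At an assumed correlation of 0.6, a baseline-adjusted analysis keeps 90% power up to a BSC gain of about 0.26 points with SD 2.155, or about 0.19 with SD 2.3. This stands, but only conditionally. The protocol states no correlation and does not claim the gain, and how much is gained depends on how baseline enters the model. A pure change-score analysis has an SD of √(4 + 5.29 − 2r × 2.0 × 2.3). At r = 0.5 this is 2.166, practically the same as the unadjusted SD; at r = 0.3 it is 2.555, which is worse.

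Three stronger readings are tempting, and the document does not support them.

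- That 90% power requires the BSC arm not to change at all. The requirement runs in one direction. If the BSC arm declined by 0.2 points, the difference would be 1.5 and power about 96%.
- That the trial has about even odds of detecting its effect. That is one scenario, an unadjusted test with an assumed BSC gain of 0.5. The document gives no BSC gain, retest effect or time effect.
- That the cited study was uncontrolled. The article quotes only its before and after values and does not say whether it had a control group. What can be said is that the contrast taken from it is a within-CPAP one.

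It may also be said that a journal article condenses the full protocol. Here, though, the article does state the basis of its sample size, and that basis is the wrong contrast for the trial.

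**Conclusion.** The point holds in this form. The arithmetic behind 59 and 148 is correct, but its effect size is a within-CPAP change standing in for the difference between CPAP plus BSC and BSC alone. The stated 90% power therefore carries an unstated assumption that the BSC arm does not improve, in a design that gives that arm active advice and the same repeated test. For the calculation as stated, power falls to about 85%, 70% and 52% at assumed BSC gains of 0.1, 0.3 and 0.5 points. With baseline adjustment at an assumed correlation of 0.6 and SD 2.155, the figures are 96%, 88% and 70%.

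The direction of the dependence is certain. The actual shortfall, if any, cannot be settled from the document, because it depends on a BSC gain and a correlation that the document does not give. The supportable conclusion is that 90% power for the randomised comparison has not been shown, not that the trial is underpowered.

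**What to change.** Keep 148 and rewrite the basis in Sample size calculation:

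- State that 59 evaluable participants per arm give 90% power (two-sided 0.05) for a CPAP-minus-BSC difference of 1.3 MoCA points with SD 2.16, 80% for 1.12, about 70% for 1.0 and about 52% for 0.8.
- State that 1.3 is a within-CPAP before-after contrast, and that using it as the between-arm difference assumes no improvement under BSC.
- Quote the power of the baseline-adjusted analysis over a range of assumed correlations, for example 0.3 to 0.7, labelled as assumptions and with the SD used.

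The cost is a change of wording and a less favourable stated power. No extra participants are needed, and the endpoint and the analysis stay as they are. Enrolment was still under way according to Trial status, so the restatement can be made before the results are known.
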